### Data Monitoring

No data monitoring committee will be installed because the risks of participation in this study is categorized as insignificantly low. A data management plan is developed, detailing data management procedures, data standards, minimal data set requirements, and protocols (Isala Institutional Research Board). Data are collected in an online data management platform (Research Manager). Data will be securely stored for at least 15 years, according to hospital Institutional Research Board storage protocols. The study sponsor will be in charge of overseeing data management and access procedures. The Research Manager software will assign a “study ID.” The reference between the study ID and the hospital patient number is listed in the patient identification log. The patient identification log will only be accessible by authorized personnel. Each electronic case report form will be completed on-site by the investigator or an authorized staff member. All imaging data will be stored on location but transferred in preparation of the multidisciplinary meeting. After the multidisciplinary meeting these data will be destroyed for privacy reasons. All individual patient data records will be collected on a confidential basis and according to the applicable national data protection, privacy, and secrecy laws.

### Safety Reporting

Adverse events are defined as undesirable experiences of a participant within 30 days after treatment and related to participation in this study. All adverse events reported by the participant or observed by the investigator or study staff will be recorded. A serious adverse event is any untoward medical occurrence, within 30 days after treatment and related to participation in this study and results in death, is life threatening (at the time of the event), requires hospitalization or prolongation of existing inpatients’ hospitalization, results in persistent or significant disability or incapacity, or any other important medical event that did not result in any of the outcomes listed above. The investigator will report all serious adverse events to the sponsor without undue delay after obtaining knowledge of the events.

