#### Control Group

The care as usual group will be offered surgery or UAE. Surgery will be either hysterectomy or myomectomy. Both hysterectomies and myomectomies can be performed by laparoscopy or laparotomy depending on the size and location of the fibroids. Participants allocated to the control group can decide together with their gynecologist which of the (minimally) invasive treatments they wish to undergo. All of the usual care treatments are performed extensively at the participating centers and will be performed according to national guidelines and local protocols. Surgery is preceded by a preoperative screening for anesthetic risk assessment. Depending on the modus of the hysterectomy or myomectomy, patients will be hospitalized for a minimum of 1-3 nights. UAE will be performed by well-trained and experienced radiologists. UAE can be either unilateral or bilateral. The patient usually has to stay in the hospital for 1-3 nights for careful pain monitoring after the procedure. Six weeks after all usual care treatments, a follow-up appointment at the gynecology department will be scheduled.

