### Data Collection

Data collection will take place before treatment, and at 3, 6, 12, and 24 months after treatment by questionnaires. Furthermore, baseline data of patient and treatment costs will be collected before treatment and after data lock-in (Table 1).

**Table 1 table1:** Timeline of data collection.

Data	Baseline	Treatment	3 months	6 months	12 months	24 months	Data lock-in
Informed consent	X						
Patient characteristics^a^	X						
Pregnancy outcomes^b^	X					X	
UFS-QoL^b,c^	X		X	X	X	X	
EQ-5D-5L^b,d^	X		X	X	X	X	
Onset of menopause^b^						X	
(Time to) reintervention^a^			X	X	X	X	X
Adverse events/complications^a^		X	X	X	X	X	
PREM^b,e^	X		X	X	X	X	
Recovery time^a^		X	X	X			
Medical Consumption Questionnaire^b,f^	X		X	X	X	X	
Productivity Costs Questionnaire^b,f^	X		X	X	X	X	
Costs of treatment^a^							X
Reason for not participating^a,g^	X						

^a^Retrieved from questionnaires and medical record.

^b^Retrieved from questionnaires solely.

^c^UFS-QoL: Uterine Fibroid Symptom and Quality of Life questionnaire.

^d^EQ-5D-5L: 5-level version of the EuroQoL Questionnaire.

^e^PREM: patient-reported experience measurement

^f^Used for the cost-effectiveness analysis.

^g^Data collected by the gynecologist in case of not willing to participate.

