#### Secondary Outcomes

Data on several secondary outcomes will be collected (Table 2). These include adverse events and complications during treatment and recovery, cost-effectiveness–relevant outcomes such as hospital stay duration and use of (co)medication, patient-reported experiences, reintervention rate in case a uterine-sparing treatment was performed, reproductive outcomes when applicable, and technical outcomes after MR-HIFU, such as NPV reached.

**Table 2 table2:** Secondary outcomes of the MYCHOICE^a^ study, including measurement tool and statistical analyses.

Outcome	Description	Measurement	Statistical analyses
QoL^b^ parameters	QoL is expected to be negatively correlated with symptom severity. When symptoms decrease, the QoL is expected to improve.	UFS-QoL^c^ questionnaire and EQ-5D-5L^d^ questionnaire.	The time course of the change in health-related quality of life after treatment will be analyzed using longitudinal covariance analysis similar to the analysis of the change in SSS^e^.
Adverse events and complications	The nature of adverse events and complications of the 2 treatment arms are expected to differ.	Adverse events will be classified according to the classification of surgical complications [32].	Adverse events are analyzed using descriptive statistics. Adverse events per treatment group and treatment will be presented with their occurrence rate.
Length of hospital stay	Reduced hospital stay is beneficial in terms of health care costs and is also considered as a great advantage by patients.	Length of hospital stay will be collected from the patient hospital file.	The average length of the hospital stay will be reported as mean (SD) or median (interquartile range).
Periprocedural and postprocedural pain	Pain perception may influence treatment experience and therefore satisfaction with the treatment.	Periprocedural and postprocedural pain will be measured on a numerical rating scale from 0 to 10 in the 3 months’ follow-up questionnaire. Pain complaints at 3, 6, 12, and 24 months after treatment will be registered by the amount and duration of pain killers used.	The numerical rating score is considered to be a semicontinuous measure (range 0-10: higher score represents more pain). Pain experienced will be reported as mean (SD) or median interquartile range.

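### The 30-day, participation-related definition of adverse events conflicts with collection to 24 months and leaves the scope of the arm-level rates undefined

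*Protocol article*

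**What the plan says.** The protocol article describes the scope of adverse events in three places.

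- **Safety Reporting.** "Adverse events are defined as undesirable experiences of a participant within 30 days after treatment and related to participation in this study". The serious category has the same limits: "A serious adverse event is any untoward medical occurrence, within 30 days after treatment and related to participation in this study". The investigator's duty to report to the sponsor attaches to serious events so defined.
- **Data Collection and Table 1.** "Data collection will take place before treatment, and at 3, 6, 12, and 24 months after treatment by questionnaires". The row "Adverse events/complications^a" is marked at treatment and at each of those four follow-up points, with no mark at baseline. Its footnote gives questionnaires and the medical record as sources.
- **Secondary Outcomes and Table 2.** The text introducing the outcomes says: "These include adverse events and complications during treatment and recovery". The Table 2 analysis is descriptive: "Adverse events per treatment group and treatment will be presented with their occurrence rate". Neither a 30-day limit nor a relatedness condition appears there.

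Three other statements bear on how the definition would work. The exclusion criteria show that some women receive leuprorelin before MR-HIFU, depending on fibroid size or Funaki type. The Recruitment section says that the study is the only route to MR-HIFU for fibroids in the Netherlands. The Control Group section describes the comparators as routine practice: "All of the usual care treatments are performed extensively at the participating centers and will be performed according to national guidelines and local protocols".

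**The concern.** A reader of the final report will take the adverse event rates as a safety comparison over the trial's follow-up. Under the Safety Reporting definition they would instead describe related events in the first month. Nothing in the article says which of the scopes governs the Table 2 rates, so two analysts could produce different safety tables from the same data and both claim to follow the plan.

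The relatedness condition is a separate problem, because it decides whether an event enters the data at all. The trial is open, so that judgement is made with the arm known. A complication of MR-HIFU is readily attributed to participation, since the woman could not have had the treatment otherwise. A complication of hysterectomy, myomectomy or embolisation can be attributed to participation (the woman was randomised to it) or to routine care (she might have had it anyway). The wording does not settle which.

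The serious event definition also sets the reporting duty. The Data Monitoring section states that there will be no data monitoring committee, so reporting by investigators to the sponsor is the main safety channel that the article describes.

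**Working it through.** The plan attaches no figure to this point, so there is nothing to reproduce. The check sets the scopes side by side and asks what happens to an event at each stage. The day-10, day-60 and month-9 events are illustrations.

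| Event | Safety Reporting definition | Table 1 schedule | Secondary Outcomes wording |
|---|---|---|---|
| Between randomisation and treatment, e.g. during leuprorelin | Outside: the window opens after treatment | No mark before treatment | Outside: starts with treatment |
| Day 10, judged related | Inside | Collected | Inside |
| Day 10, judged unrelated to participation | Outside | Collected | Inside: no relatedness condition |
| Day 60 | Outside | Collected at 3 months | Depends on how long recovery lasts |
| Month 9 | Outside | Collected at 12 months | Depends on how long recovery lasts |

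1. **Late events.** The 3-month collection can recover events from the first 30 days by recall or from the record. The 6-, 12- and 24-month collections ask about periods that start after day 30. No event that is new in those periods can meet the definition, so three of the five marks in the Table 1 row have no new adverse event to collect.

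2. **What recovery means.** Table 1 collects recovery time at treatment, 3 months and 6 months. The Secondary Outcomes wording therefore cannot be assumed to mean 30 days, and it remains a third scope.

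3. **Pretreatment.** The article distinguishes pretreatment with leuprorelin from the MR-HIFU that follows it. A window that opens after treatment does not cover it, and neither does the Table 1 row. The article describes this exposure only in connection with MR-HIFU.

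4. **Relatedness.** Table 2 wants rates for each arm and each treatment, so control treatments are expected to generate counted events. The definition makes counting conditional on a link to participation and does not say whether receiving a randomised usual-care treatment is such a link.

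5. **Reporting duty.** Because the serious definition repeats both limits, a serious event in the first or last two rows of the table, or one in the third row, carries no stated duty to report.

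6. **Size.** The number of events lost cannot be calculated, because the article gives no complication rates by time or by arm.

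**The case against.** The best defence is that the Safety Reporting section governs reporting to the sponsor, while Tables 1 and 2 govern the outcome. On that view complications are collected to 24 months under their own heading and only the adverse event label stops at day 30. This may be the intent, but the article does not say so. Table 1 puts both terms in one row, Table 2 puts them under one outcome with one classification, and the Safety Reporting wording is an unqualified definition.

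It can also be said that other data soften the loss. Reinterventions due to complications are collected to 24 months, menopause and reproductive outcomes at 24 months, and complications are recorded prospectively for costing. That stands, but none of these feeds the adverse event rate. A condensed article may fairly leave details of pretreatment events to the full protocol. It is still a problem that the definition it does print excludes them.

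Several stronger readings are tempting and are not supported:

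- **Control-arm complications would be undercounted, perhaps almost all of them.** This requires reading participation as excluding the randomised control treatment. The planned rates per treatment point the other way. The 30-day limit applies to both arms, and the leuprorelin gap would lower the MR-HIFU count. No net direction follows.
- **Only about 4% of events are covered.** Thirty of roughly 730 days is about 4% of the follow-up time. It says nothing about the share of events.
- **Visits after day 30 cannot capture events.** The control clinic visit ("Six weeks after all usual care treatments, a follow-up appointment at the gynecology department will be scheduled") falls at day 42, but the window concerns when an event occurs. A later visit can record an earlier event.
- **Embolisation harms appear late.** The Introduction lists such harms without giving their timing.
- **The rates will be formally compared.** Table 2 plans descriptive presentation only.

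**Conclusion.** The contradiction holds on the face of the text. The Safety Reporting definition cannot be applied together with the Table 1 schedule or the Secondary Outcomes wording, and the article does not say which prevails. Taken literally, new events after day 30 and events between randomisation and treatment are neither counted as adverse events nor covered by the duty to report serious events.

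That the arm-level rates could be distorted is a possibility, not a demonstrated bias. It rests on the assumption that investigators, knowing the arm, may judge relatedness to participation differently for MR-HIFU and for usual care. Neither direction nor size can be determined from the article.

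The consequence is confined to a descriptive secondary outcome and to safety reporting. The primary symptom severity comparison and the sample size do not depend on it. An amendment is worthwhile because safety is part of the case made for MR-HIFU and the correction is cheap.

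**What to change.** Reconcile the Safety Reporting section, Table 1 and the adverse event entry under Secondary Outcomes:

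1. Use one scope for adverse events and complications in both arms, running from randomisation through pretreatment and treatment to the 24-month collection that Table 1 already schedules.
2. Record relatedness to the assigned treatment, including any pretreatment, as a separate field, and remove relatedness to participation as a condition of entry.
3. In Table 2, report events up to day 30 after treatment as a prespecified subset alongside the full-period rates.
4. Bring the serious event definition into line, so that the reporting duty covers the same period. If a narrower period for expedited reporting is intended, state it as a reporting rule separate from the definition.

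The cost is a wording amendment and somewhat more event recording and coding, because events that are unrelated, late or before treatment would now be entered. Collection to 24 months needs no new contact. The time between randomisation and treatment needs an added mark in Table 1. The case report form is not shown, so the exact change to it cannot be specified here.

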### Auditing

The clinical monitor will be responsible for verifying adherence to the protocol, reviewing participant records and source data, maintaining records of all actions taken to correct protocol deficiencies during the investigation, and assuring that the data needed to complete the study are complete and accurate.

### Patient and Public Involvement

The Foundation Bekkenbodem4All (Pelvicfloor4All) was consulted on the design of the study from a patient perspective and their opinion and feedback were taken into consideration. In addition, an evaluation meeting with previous MR-HIFU patients took place. Outcomes of this meeting were used to improve MR-HIFU treatment routine and to point out important patient outcomes. During inclusion, Bekkenbodem4All will promote the study via their network and participate in the yearly meetings in which the progression of the study is discussed. When the results of the study warrant uptake of the treatment in standard reimbursed care, they will aid in the final implementation of the treatment.

### Ethics Approval

This protocol, informed consents, and patient information have been approved by the local medical ethical committee of Isala Hospital (NL74716.075.20) on September 24, 2020, with respect to scientific content and compliance with applicable research and human patient regulations. The research activities of the MYCHOICE study comply with the international conventions and codes of conduct, and the latest Helsinki Declaration of the World Medical Association adopted by the World Medical Assembly.

### Dissemination Policy

We aim to make all data Findable, Accessible, Interoperable and Reusable (FAIR) according to the FAIR principles [37]. Therefore, we will assign all (meta)data with a unique and persistent (global) identifier and register or index them in a searchable digital data repository at the end of the study for long-time archiving and data reuse purposes. Results will be presented in (inter)national congresses and meetings, and will be published in peer-reviewed journals, publications of the patient associations, in health-related journals, and on various websites such as the MYCHOICE study website.

## Results

Inclusion for the MYCHOICE study started in November 2020. Patient enrollment is expected to last approximately 36 months. Because of the 24-month follow-up, we expect to complete data collection in 2026 and plan the dissemination of the results subsequently.

## Discussion

### Added Value of MYCHOICE

The MYCHOICE study distinguishes itself from previous MR-HIFU trials in that it is an RCT in which full ablation protocols and the latest MR-HIFU equipment are used for uterine fibroid treatment. Moreover, patient follow-up is 24 months. Furthermore, it answers important research questions on both effectiveness and cost-effectiveness with outcomes that are relevant for policy makers, physicians, and patients.

### Strengths

As a primary outcome, we will use QoL in terms of symptom reduction 24 months after treatment. We did not choose the commonly used outcome in uterine fibroids studies, reintervention rate, as our primary outcome because re-interventions are not expected to occur after hysterectomy. Symptom reduction will most likely also differ between hysterectomy and uterus-saving treatment options. However, the influence of symptom reduction after hysterectomies in the control group is probably limited, because we expect that most women who will participate in the MYCHOICE study prefer a uterus-preserving treatment option, just like the intervention under study. This is further enhanced by the 2:1 randomization ratio. This ratio will lead to a higher chance to undergo MR-HIFU treatment, and we believe is therefore an important strength of the design. Another strength is the fact that this unbalanced design will enable us to gather more data on our intervention, while the effectiveness of standard care is already much better documented.

Our follow-up duration of 24 months is based on the long-term outcomes of a retrospective study on MR-HIFU treatment results performed by our group [14]. In this study, we found that all reinterventions were performed within 24 months after the initial treatment, indicating that the treatment effect reaches a steady state within 24 months after treatment. Thus, it is not useful to prolong follow-up of these patients.

### Limitations

A possible limitation of the MYCHOICE study is the uncommon use of a mixed control group. However, in current daily practice, usual care for women with symptomatic uterine fibroids in whom conservative treatment failed or is undesired consist of several (minimally) invasive treatments. The minimally invasive UAE is reimbursed in the Netherlands, and would therefore be an appropriate reference treatment for the noninvasive MR-HIFU treatment. However, hysterectomies are by far the most frequently performed and should thus not be omitted from the standard care group. The standard care group is complemented with myomectomies. We expect that women willing to participate in this study are mostly searching for a uterus-saving treatment option, sometimes because of a future pregnancy wish. For this category of women, myomectomy is the only alternative and therefore a mixed control group qualifies the most. By using this mixed group, we believe we best represent the real-world situation. Furthermore, the information on treatment preference in the control group can be used to gain more insights into patient preferences.

Although an RCT design is commonly considered to provide the best evidence on the effectiveness of a new intervention compared with usual care, our RCT design also poses several challenges [38]. Women may not be willing to be randomized, which may delay enrollment, and our 2:1 randomization ratio with a mixed control group may lead to low sample sizes for the individual treatment options in the mixed control group, which will limit valid comparisons between outcomes of individual treatments. However, sufficient data on primary outcomes are already available for all treatments in this control group. Other possible limitations of the MYCHOICE study are that not all (secondary) outcomes are equally relevant for all included treatments and that the MR-HIFU treatment cannot be performed in all participating centers. However, because of the restricted number of patients eligible for treatment and the complexity of the treatment, it might not be cost efficient to have more than 2-4 uterine fibroid MR-HIFU facilities in the Netherlands.

## Abbreviations

EQ-5D-5L: 5-level version of the EuroQoL questionnaire
FAIR: Findable, Accessible, Interoperable and Reusable
IDEAL: Idea, Development, Exploration, Assessment and Long-term study
iMCQ: iMTA Medical Consumption Questionnaire
iPCQ: iMTA Productivity Cost Questionnaire
MR-HIFU: magnetic resonance image–guided high-intensity focused ultrasound
MRI: magnetic resonance imaging
MYCHOICE: MYoma treatment Comparison study: High-intensity image–guided fOcused ultrasound versus standard (minimally) Invasive fibroid care—a (Cost-)Effectiveness analysis
NPV: nonperfused volume
PREM: patient-reported experience measurement
QoL: quality of life
RCT: randomized controlled trial
SPIRIT: Standard Protocol Items: Recommendations for Interventional Trials
SSS: symptom severity score
UAE: uterine artery embolization
UFS-QoL: Uterine Fibroid Symptom and Quality of Life questionnaire
